### Sample size calculation

The sample size for this cluster RCT has been computed based on methods described in Donner et al. [36]. We made several assumptions from the existing knowledge about the study population while calculating the sample size for this cluster RCT. Specifically, our sample size calculation is balanced between a standard statistical power and a pragmatic study setting. Based on our pilot data and existing literature we predict a 35% improvement of HRQoL in the IMCBR group, 20% improvement in the CBR alone group, and 5% improvement in the care-as-usual group [9]. A homogeneous study population will allow us to balance randomisation considering intra-cluster correlation of 0.5 and coefficient of variation in cluster size of 0.5.

Based on the calculation, we will recruit seven clusters in each arm (allocating 1:1:1), and each cluster will consist of 10 children with CP- primary caregivers dyads totalling 21 clusters of 210 dyads. With a sample size of 210 dyads, this study will have 80% statistical power to detect these effects (two-sided α-value = 0.05). Power calculation took into account up to 20% sample attrition by the end of the trial.

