### Outcome measures

The following outcomes will be measured at baseline, 6 months, 12 months, and 18 months.

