### Secondary and exploratory outcomes

1. Motor function of children with CP

*Gross Motor Function Measure (GMFM)-66*: The GMFM-66 is designed to assess the gross motor function in children with CP and measure changes over time. It is a valid and reliable tool comprising 66 items, subset of the 88 items included in original GMFM-88 developed based on the Rasch analysis to define the “gross motor function” of children with CP [47, 48]. The 66 activities in GMFM-66 cover five dimensions; (a) lying and rolling, (b) sitting, (c) crawling and sitting, (d) standing, and (e) walking, running and jumping.

*Gross Motor Function Classification System (GMFCS)*: The GMFCS is a five-level classification of functional motor abilities of children with CP. The Level I indicates minimal functional deficits among children with CP, whereas the level V indicates the highest level of functional deficits among children with CP [49].

*Classification of CP based on motor function and topographical distribution*: The predominant motor type i.e. spastic CP and non-spastic CP (dyskinesia, ataxia and hypotonia) and topographical distribution i.e. monoplegia, hemiplegia, diplegia, triplegia, and quadriplegia will be assessed following the BCPR protocol [3].

2. Communication function of children with CP

*Communication Function Classification System (CFCS)*: The CFCS is a validated tool to categorise children’s communication skills into five mutually exclusive levels of everyday communicative function. Classifications are made according to the descriptions of the levels and the distinctions between them [50, 51].

3. Nutritional status of children with CP

Anthropometric measurements will be taken using standard guidelines of WHO and will be analysed to assess the nutritional status of children. The following measurements will be collected at each assessment; (a) weight in kilograms, (b) height in centimetre (cm), (c) mid-upper arm circumference in cm, (d) skin-fold thickness in millimetre, and (e) head-circumference in cm.

4. Mental health of primary caregivers of children with CP

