### Statistical methods

Data will be collected using paper-based forms. Research data will be anonymised and stored securely and separately for participant identifiable information. This will include monitoring secure data transfer from field to central office, data entry and quality control of completed forms, query about missing or invalid data and archiving of physical forms. Data will be collected using validated questionnaires. Data will be entered using Microsoft Access or SQL Server as the relational database engine. Any error identified during data entry or in data cleaning will be logged for field supervisor assessment and will be resolved after proper field verification. The physical data will be stored for seven years in a locked cabinet at head office of CSF Global based in Bangladesh as per national and international guidelines.

For statistical analysis, we will import the dataset into Stata 17. Primarily, we will perform an intention-to-treat analysis. Since our primary endpoint (i.e. HRQoL) will have continuous data, we will perform a mixed effect model (e.g. generalised linear mixed model) to calculate the effect of intervention according to the components of TAPQoL. We will also compare the TAPQoL scores between the three arms, and assess the differences using appropriate tests. Our proposed models will include the intervention arm as a fixed effect and study samples in each cluster as a random effect to explain cluster effects. To account for the intra-cluster correlation in calculating 95% CI and p-value, we will use a Sandwich estimate of standard error.

Baseline characteristics will be compared (as part of data matching) and adjusted using appropriate regression models. Descriptive statistics (frequencies, means and 95% confidence intervals) will be used to describe the sample at baseline and post-intervention. All analyses will be conducted using a significance level set at p<0.05. Data visualisation will be done using R Studio version 4.1.0.

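### Baseline adjustment is tied to a comparison of arms and to matching, with no commitment to baseline TAPQOL; prespecifying it would cost nothing and may gain precision

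*Protocol article*

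**What the plan says.** All of the analysis wording is in the Statistical methods section of the protocol article.

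- **Model type.** For the continuous primary outcome, "we will perform a mixed effect model (e.g. generalised linear mixed model) to calculate the effect of intervention according to the components of TAPQoL".
- **Named terms.** "Our proposed models will include the intervention arm as a fixed effect and study samples in each cluster as a random effect". I read the second term as a random effect for cluster.
- **Standard error.** "we will use a Sandwich estimate of standard error".
- **Baseline.** "Baseline characteristics will be compared (as part of data matching) and adjusted using appropriate regression models".

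No covariate is named. The section on outcome measures says: "The following outcomes will be measured at baseline, 6 months, 12 months, and 18 months". A baseline TAPQOL score will therefore exist for each child assessed at entry. GMFCS level is also collected, and appears among the secondary and exploratory outcomes: "The GMFCS is a five-level classification of functional motor abilities of children with CP". The sample size section gives seven clusters per arm with 10 dyads each, an intra-cluster correlation of 0.5, a coefficient of variation of cluster size of 0.5, and up to 20% attrition.

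**The concern.** Randomisation makes the arms comparable in expectation, so a baseline comparison is neither a test of anything useful nor a sound basis for choosing covariates. Matching belongs to observational studies. A covariate should enter because it is expected to predict the outcome, and it should be chosen before the data are seen. The baseline value of the outcome is the natural first candidate.

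Two things are at stake. First, the wording allows the covariate set to be settled after the baseline table is known. With seven clusters per arm, chance imbalances can be sizeable, and the choice of covariates can move the estimate. Second, if baseline TAPQOL does not end up in the model, a possible reduction in the standard error is given away in a trial with few clusters.

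**Working it through.** **The plan's own figure.** The article gives no figure for the effect of adjustment. The nearest is the 80% power in the sample size section, for improvements of 35%, 20% and 5%. No standard deviation is given, so I read these as proportions (an assumption).

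- Design effect = 1 + ((1 + CV²)m − 1) × ICC. With m = 8 after 20% attrition: 1 + (1.25 × 8 − 1) × 0.5 = 5.5.
- Effective number per arm = 56 / 5.5 = 10.2.
- Power: 39% (35% vs 5%), 11% (35% vs 20%) and 17% (20% vs 5%).

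The 80% does not reproduce on this reading. That is a separate matter and nothing below depends on it, but for this reason I express the gain as a change in standard error and not as power.

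**Inputs for the gain.** ICC = 0.5 and seven clusters per arm (article); m = 8 (10 less 20%), with equal cluster sizes for simplicity. The baseline to follow-up correlations between clusters (rb) and within clusters (rw) are not in the article; I assume 0.3 to 0.8.

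**Formula.** Up to a common factor, the variance of a cluster mean is

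- unadjusted: ICC + (1 − ICC)/m = 0.5 + 0.0625 = 0.5625
- adjusted: ICC(1 − rb²) + (1 − ICC)(1 − rw²)/m

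The standard error ratio is the square root of adjusted over unadjusted.

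| r | Equal at both levels: SE cut | Between clusters only: SE cut | Within clusters only: SE cut |
|---|---|---|---|
| 0.3 | 5% | 4.1% | 0.5% |
| 0.5 | 13% | 11.8% | 1.4% |
| 0.6 | 20% | 17.5% | 2.0% |
| 0.8 | 40% | 34.3% | 3.6% |

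Examples at r = 0.5. Equal at both levels: ratio √(1 − 0.25) = 0.866. Within only: (0.5 + 0.0625 × 0.75)/0.5625 = 0.972, and √0.972 = 0.986. At an ICC of 0.5, 0.5/0.5625 = 89% of the variance of a cluster mean lies between clusters, so the gain comes almost wholly from the between-cluster correlation.

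**Small number of clusters.** The table ignores the cost of estimating the slope. A simulation of two arms of seven clusters, with r equal at both levels, gave these standard errors in SD units:

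| r | Unadjusted | Adjusted | Change |
|---|---|---|---|
| 0.3 | 0.402 | 0.405 | +0.7% |
| 0.5 | 0.407 | 0.364 | −10.6% |
| 0.6 | 0.387 | 0.325 | −16.0% |
| 0.8 | 0.404 | 0.256 | −36.6% |

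This agrees with theory. Estimating one slope from 14 cluster means multiplies the expected variance by 1 + 1/(14 − 4) = 1.1, and the standard error by 1.049. At r = 0.3 the net ratio is 0.954 × 1.049 = 1.00, so nothing is gained. A slope shared by all 21 clusters costs less (1 + 1/16 = 1.0625, or 1.031 on the standard error), which leaves about 2% at r = 0.3: 0.954 × 1.031 = 0.983.

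**The case against.** The best defence is that this is a condensed article and that a full protocol or analysis plan may fix the covariates. That stands for much of what one might ask. The covariate list and the visit, arm-by-visit and child-level terms are ordinary analysis-plan content, and I do not count their absence as a finding.

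Several stronger readings are tempting, and the text does not support them.

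- **The model contains only arm and cluster.** The sentence says what the models include, not that this is everything. The next paragraph of the same section promises some baseline adjustment, and the section on concurrent interventions says that use of local services will enter the analysis.
- **Adjustment happens only if the arms differ.** The sentence says compared and adjusted. It states no condition, threshold or selection step. The fair reading is that the two are tied together and the choice is left open.
- **The arm effect will be diluted because baseline scores are pooled with follow-up.** A reader might infer this from four assessments and a single named fixed effect. Nothing says that baseline scores will be entered as outcomes, so this is a possibility to close off and not an error in the plan.
- **Precision is lost.** Nothing excludes baseline TAPQOL from the adjustment, and the gain from including it can be close to nil.

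What the defence does not answer is the adjustment sentence itself. It is in the document, it is poorly chosen for a randomised trial, and an analysis plan that followed it would carry the problem forward.

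**Conclusion.** The point holds in limited form. The one stated rule for baseline adjustment rests on comparing arms and on matching, and does not commit to baseline TAPQOL. Covariate choice is left open to what the comparison shows, and some precision may be forgone.

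The size is conditional. At an ICC of 0.5 with r equal at both levels, the large-sample reduction in standard error runs from about 5% (r = 0.3) to 40% (r = 0.8). With 14 clusters, the reduction at r = 0.3 disappears. If baseline predicts only within clusters, it is 0.5% to 4% throughout. All correlations are assumptions. This is an improvement available without cost, not a demonstrated bias.

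**What to change.** In Statistical methods:

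1. Delete the matching wording, and delete baseline comparison as a basis for adjustment. State that baseline characteristics are shown by arm descriptively only.
2. Prespecify that the primary mixed model of follow-up TAPQOL includes the baseline value of the same TAPQOL score as a covariate, whatever the baseline table shows, alongside arm and the cluster random effect. Baseline GMFCS level may be added if it is named in advance; with so few clusters the list should stay short.
3. State that baseline TAPQOL enters as a covariate and not as an outcome row, so that it cannot dilute the arm effect.

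If an analysis plan already does this, align the article's sentence with it. The cost is wording only: both measures are already collected at baseline, and design, sample size and conduct do not change.

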### Trial monitoring

An independent Data Safety and Monitoring Board (DSMB) has been formed for this trial. The members of DSMB will meet monthly to monitor the safety of trial participants and the quality of trial data. The Chair of the DSMB will report to the Chief Investigator regarding issues related to data safety, quality of intervention and serious adverse event.

A serious adverse event will be defined as any event that results in injury, requires inpatient hospitalisation or prolongation of existing hospitalisation, or death or results in a persistent or significant disability or incapacity.

The DSMB will conduct a blinded interim analysis of effectiveness and safety endpoints once 210 participants have completed the trial. The DSMB may recommend continuing the trial, early termination of the trial, or modification of the trial. A recommendation to terminate the trial early will be made if there is clear evidence of a clinically harmful effect. The trial will not be stopped early on the grounds of futility.

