## Introduction

Cerebral palsy (CP) is a group of non-progressive neurological disorders caused by damage to the developing brain [1]. The prevalence and severity of CP are considerably higher in low- and middle-income countries (LMICs) compared with high-income countries (HICs) [2–4] and diagnosis is likely to be delayed [3]. Early diagnosis of children with CP and access to evidence-based early interventions such as community-based rehabilitation (CBR) are key to improving the long-term health-related quality of life (HRQoL) [5], motor function [6], cognitive [7], and other health outcomes in children with CP. However, the majority of such evidence is from HICs [8, 9]. Randomised controlled trials (RCTs) testing the effectiveness of CBR programs for children with CP in LMICs are relatively scarce. Moreover, these interventions rarely consider issues pertinent in the lives of children with CP and their ultra-poor families in LMICs.

In LMICs, many families of children with CP are ultra-poor, which contributes to poor health care access, delayed diagnosis, delayed intervention, overall poor health and wellbeing, and long-term reduced effectiveness of rehabilitation therapies [3, 10–15]. Our last 16 years of research in rural Bangladesh, which led to the development of the Bangladesh CP Register (BCPR—first ongoing population-based CP register in LMICs) [16], confirms that diagnosis of CP is delayed [17] and there is limited or no access to evidence-based rehabilitation programs in rural Bangladesh [18]. The average age at diagnosis of CP in Bangladesh is 5 years compared to 1.5 years in HICs [2, 3]. We also found that even when rehabilitation programs were available, access to care was negatively impacted by poverty [3, 14]. In Bangladesh, 97% of families of children with CP live below the poverty line [3]. Moreover, people with disability and their families are often excluded from economic activities [19]. These families struggle to meet basic needs and their child’s rehabilitation often does not feature high on the agenda. Therefore, an integrated approach combining the physical rehabilitation of children with CP and the economic empowerment of their family is required for tangible long-term improvements.

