Goal selection: The CBR session will start with realistic and appropriately time-framed goals set up in collaboration with parents. Goals are basically some specific tasks that are needed for everyday life and which children with CP find challenging. These tasks could be gross motor, self-care, communication, play, or school-based activities.Assessment: A detailed assessment will then be carried out to identify facilitating and limiting factors in achieving the goals. This will involve assessing the physical requirements of the selected task, the resources and equipment that are needed, and the settings in which the task is done. Both goal selection and assessment session will be facilitated by an experienced physiotherapist.Intervention: Weekly group therapy sessions will be conducted by two Community Rehabilitation Officer (CROs). The CROs hold a certificate level course on basic CBR techniques and have five years of experience in community-based management of children with CP. The CROs will guide parents/primary caregivers to scaffold the selected motor tasks, so that the child could actively complete at least a part of the task. Parents will be encouraged to use their knowledge of their child’s play preferences to elicit self-generated motor activity. Modified constraint induced movement therapy and/or bimanual training will be used when asymmetrical hand function is evident. CROs will also assist parents to set up a motor-enriched play environment at home to promote child’s self-generated movements, exploration, and task success. Parents will be advised to practice through joyful play until the main goal is achieved.Outcome evaluation: CROs will evaluate the compliance to the intervention by weekly follow-up phone calls weekly and monthly home visits. The attendance to group sessions and compliance to intervention will be monitored daily by a physiotherapist to ensure adherence to intervention. The extent to which a child’s goals are achieved will be monitored and recorded.

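### The serious adverse event definition counts any injury, with no severity threshold, and has no life-threatening trigger, so some life-threatening events in survivors fall outside it

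*Protocol article*

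**What the plan says.** The Trial monitoring section of the protocol article states: "A serious adverse event will be defined as any event that results in injury, requires inpatient hospitalisation or prolongation of existing hospitalisation". The sentence goes on to name two more triggers: death, and disability or incapacity that is persistent or significant. That gives four triggers: injury, admission or prolonged admission, death, and disability or incapacity.

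The same section sets out how safety is overseen: "The members of DSMB will meet monthly to monitor the safety of trial participants and the quality of trial data". The DSMB Chair reports to the Chief Investigator on matters that include serious adverse events. On early stopping it says: "A recommendation to terminate the trial early will be made if there is clear evidence of a clinically harmful effect".

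Three statements elsewhere bear on the definition:

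- The Introduction says that ultra-poverty "contributes to poor health care access, delayed diagnosis, delayed intervention", among other effects.
- Cluster formation and randomisation gives high mortality in children with cerebral palsy below five years as one consideration behind the 1:1:1 allocation.
- The Goal Directed Training text, under Arm A, describes weekly group sessions, weekly follow-up calls, monthly home visits and more active movement at home: "CROs will also assist parents to set up a motor-enriched play environment at home to promote child’s self-generated movements".

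**The concern.** The definition looks too wide at one end and too narrow at the other. Injury is the only non-fatal trigger with no limit on severity: hospitalisation must be inpatient, and disability or incapacity must be persistent or significant. Meanwhile, an event that put the child's life at risk does not count as serious on that ground alone. It must also cause injury, admission, or disability or incapacity of the stated kind.

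At stake is what the word serious means in this trial's safety record. It is the only adverse event category that the article defines, and one of the matters that the DSMB Chair reports on. In families with poor access to care, a severe event that does not lead to admission is plausible. A category that takes in trivial injuries but can leave out a near-fatal episode is a poor summary of harm, and more so if minor injuries are noticed more often in some arms than in others.

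**Working it through.** No calculation applies to the definition itself. The check is to apply each trigger literally and then look through the rest of the article for anything that changes the result.

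**Step 1: the qualifier on each trigger.**

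| Trigger | Qualifier in the text |
|---|---|
| Injury | none |
| Hospitalisation | inpatient, or prolonging an existing stay |
| Death | none needed |
| Disability or incapacity | persistent or significant |
| Life-threatening event | trigger not listed |

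The opening words, "A serious adverse event will be defined as any event that results in injury", place no limit on injury. The list closes with "or death or results in a persistent or significant disability or incapacity", and nothing follows. No other section adds a severity threshold or a life-threatening criterion.

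**Step 2: two cases read against the list.**

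- *A bruise from a fall during motor practice.* It results in injury, so it is serious.
- *A choking episode managed at home, with full recovery.* Injury: no. Admission: no. Death: no. Persistent or significant disability or incapacity: no. It meets no trigger, so it is not serious.

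**Step 3: the limits of the gap.** A life-threatening event that also causes injury, leads to admission, or leaves persistent or significant disability or incapacity is still caught. What is missed is a life-threatening event in a survivor that does none of these.

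**Step 4: relevance to this trial.** Eligibility is restricted to ultra-poor families and to children aged five or under. The article's own statements on access to care and on mortality under five therefore describe the enrolled group. The first makes admission an incomplete marker of severity. The second makes life-threatening events a realistic possibility.

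**Step 5: contact by arm.** Arm A has weekly sessions, weekly calls and monthly home visits. Arm B's sessions are described as identical to arm A's rehabilitation component, so the same follow-up is taken to apply there. Arm C gets initial education and then, as far as the article describes, only the outcome assessments at 6, 12 and 18 months that all arms share. Staff therefore have more occasions to hear of a minor injury in A and B. The article does not say that adverse events are collected at those contacts, so uneven reporting is a possibility and not a demonstrated result.

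**The case against.** The strongest case on the other side has four parts.

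**The last trigger is broader than lasting disability.** It reads persistent *or* significant, and it includes incapacity. A prolonged seizure at home might qualify as significant incapacity even if it passes. This stands. It narrows the gap, and it is why the choking example is the safer one.

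**The DSMB is not confined to events labelled serious.** A reader might infer that the serious-event count drives the harm rule, or that minor injuries will dominate what the board sees. The article supports neither. The stopping ground is clear evidence of clinical harm, with no count or threshold; the monthly remit is the safety of participants in general; and the route by which events reach the board is not described. The article also gives no injury rate for any arm, so a projected number of minor events would be invented. A board exercising judgement could discount bruises and could hear of a choking episode. This stands as a limit on the consequence. It does not repair the definition.

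**A wide injury trigger is the cautious error.** It is the one broad acute trigger that needs no admission. Narrowing it carelessly could remove real injuries treated at home, such as an uncomplicated fracture. This stands, and it governs how the fix is worded.

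**The article is condensed.** Severity grading, forms and escalation may sit in a fuller protocol or a DSMB charter. That is fair for those items. It does not cover the definition, which the article states in full.

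**Conclusion.** The point holds as a defect in a stated definition: injury has no severity threshold, and a life-threatening event is not serious in its own right. The first fault lets trivial events in. The second leaves out life-threatening events in survivors who have no injury, no admission and no persistent or significant disability or incapacity.

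The size cannot be given as a number, because the article reports no rate of injury or of life-threatening events. Nothing changes in the sample size, the power or the primary analysis. The case for acting rests on the article's own statements about poor access to care and high mortality under five. The concern about uneven reporting between arms rests on the further assumption that injuries come to light at the extra contacts in arms A and B.

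A reader might also infer that the trial's serious-event rate could not be set beside that of other trials. The article says nothing about how other trials define the term, so that is not claimed.

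**What to change.** Make two changes to the sentence in Trial monitoring.

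1. Add a separate trigger: *is life-threatening, whether or not the participant is admitted*. This can be done without touching the injury wording, and it matters more.
2. Put a severity qualifier on injury, for example *significant injury*. The sponsor and the DSMB should set the threshold so that serious injuries treated outside hospital still count. Record other injuries as non-serious adverse events so that they are not lost.

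The cost is one sentence and the matching report form. The downside is small: field staff must judge severity, and the DSMB can check those judgements at the monthly meetings it already holds.

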### Cluster formation and randomisation

The study will include 21 clusters randomised to three arms (7 clusters each) and allocated by a 1:1:1 ratio. While deciding the allocation ratio of 1:1:1 we considered the number of children with CP available in the BCPR sampling frame as well as the high mortality rate among children with CP below five years of age [37]. Each cluster will come from a ‘Mouza’, the smallest public administrative unit in Bangladesh comprising of approximately five villages (~8,250 people) and will include 10 CP child-primary caregiver dyads. In order to minimise ‘contamination’ of the intervention types, clusters will be separated from each other by buffering areas comprising villages not taking part in the study. Cluster margins will be configured so that they align with natural divisions that separate residents in the community (e.g. rivers). The randomisation process will be executed following the standard process.

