### Blinding

The interventions will be open to participants and investigators, however, the outcome assessments will be observer blinded. An independent team, informed on the purpose and importance of blinding for this study, will conduct outcome assessments. The assessors will be masked/blinded about the interventions and the outcome assessment questionnaire will be designed in a manner that does not disclose the intervention.

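### The DSMB must recommend stopping on clear evidence of harm, but the only safety analysis described is blinded and no access to arm identity is stated

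*Protocol article*

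**What the plan says.** All the monitoring text is in the Trial monitoring section of the protocol article.

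- Routine review: "The members of DSMB will meet monthly to monitor the safety of trial participants and the quality of trial data". The text does not say whether the board sees these data by arm, by code or pooled.
- Planned analysis: "The DSMB will conduct a blinded interim analysis of effectiveness and safety endpoints", set for the point at which 210 participants have finished. The word blinded is not defined.
- Powers: "The DSMB may recommend continuing the trial, early termination of the trial, or modification of the trial".
- Ground for stopping: "A recommendation to terminate the trial early will be made if there is clear evidence of a clinically harmful effect". Stopping for futility is ruled out: "The trial will not be stopped early on the grounds of futility".
- Death is part of the definition of a serious adverse event in the same section.

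Two other sections bear on this. Cluster formation and randomisation sets three arms of seven clusters at 1:1:1 and refers to "the high mortality rate among children with CP below five years of age", without giving a rate. Blinding says: "The interventions will be open to participants and investigators, however, the outcome assessments will be observer blinded".

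**The concern.** The stated rule and the stated analysis do not fit together. The rule asks whether something harmful is happening, which in a trial with an untreated comparator means that an intervention arm is doing worse than it should. The analysis that covers safety endpoints is described as blinded, and nothing in the text gives the board the arm labels.

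The protocol expects substantial mortality in this age group, so deaths are likely in every arm. A total alone then says little, and a difference without labels can mean opposite things. Blinding the board also protects little, because participants and investigators already know the allocation. The people whose masking matters are the outcome assessors, and the Blinding section deals with them separately.

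What is at stake is whether the board could recognise harm in one arm, and name that arm, from the analysis the protocol describes.

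**Working it through.** **Inputs from the protocol article.** Three arms × 7 clusters × 10 dyads = 210, which agrees with the stated total, so there are 70 children per arm. Allocation is 1:1:1. No mortality rate and no numerical harm boundary are given.

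**Step 1: what each reading of blinded lets the board see.**

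- *Pooled data.* The board sees one overall rate. As an illustration, 16 deaths among 210 children is 16/210 = 7.6%. No comparison between arms is possible.
- *Coded arms.* Suppose the 16 deaths fall as 10, 3 and 3 in three coded arms of 70 (an invented split). The chi-square p-value is 0.036, ignoring clustering, so the board sees a difference. The arms are equal in size, so size does not reveal identity. The three labels can be assigned to the codes in 3! = 6 ways. The arm with 10 deaths is care-as-usual in 2 of these, where the interventions look protective, and an active arm in 4, where an intervention looks harmful. Only the latter would point towards the harm rule.

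Under either reading, the blinded analysis does not supply the direction that the rule needs.

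**Step 2: does the size of the signal depend on blinding?** Assume mortality p over the trial of 3%, 5% or 8% (the protocol gives no figure), doubled in one arm.

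- Expected deaths with no harm: 210p. With harm: 140p + 70 × 2p = 280p.
- Pooled test: one-sided 5% binomial test of the total against a background rate p that is taken as known exactly.
- By-arm test: one-sided 5% Fisher test, affected arm (70) against the other two combined (140), or against one other arm (70). Clustering is ignored.

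| Assumed p | Expected deaths, no harm → harm | Pooled count detects | By arm, 70 v 140 | By arm, 70 v 70 |
|---|---|---|---|---|
| 3% | 6.3 → 8.4 | 14% | 19% | 10% |
| 5% | 10.5 → 14.0 | 24% | 28% | 21% |
| 8% | 16.8 → 22.4 | 39% | 45% | 34% |

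The pooled column is flattered, because the background rate would not in fact be known exactly. Clustering would normally lower the by-arm columns. Detection is low throughout because deaths are few, so these figures do not argue for unblinding. What by-arm data add is the identity of the affected arm and the direction of the effect.

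**Step 3: when the blinded analysis takes place.** It is triggered at 210 completers, and 210/210 is the whole planned sample. With the 20% attrition that the sample size section allows for, 210 × 0.80 = 168 would complete and the trigger would not be reached. Unblinding that analysis alone would therefore protect no participant still under treatment. Any gain in safety has to come through the monthly meetings.

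**The case against.** The strongest reply is that the harm rule is not tied to the interim analysis. The same section has the board meeting monthly on safety and does not say that those meetings are blinded. The sentence on termination follows the interim sentence but is not limited to it. This stands. A reader might infer that the trial cannot detect harm at all, or that a real harm would go unrecognised; the text does not support that. It supports only the narrower statement that the one safety analysis described is blinded, and that no access to arm identity is stated for it or for the monthly meetings.

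A second reply is that a board seeing an imbalance between coded arms can ask for the codes, and that a charter, which is not shown, may say how. This also stands in part, and the absence of charter detail from a journal article is not a fault. But the article does more than stay silent: it specifies a blinded analysis. A charter giving the board arm-level data at that analysis would have to be reconciled with it.

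A third reply is that low pooled power proves nothing, because by-arm power is also low. That is correct, as Step 2 shows. A reader might take 14/24/39% as the cost of blinding, but most of the shortfall comes from small numbers of deaths.

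Two further inferences go too far. The board does not itself stop the trial; it must recommend stopping. And the absence of a futility stop does not show that effectiveness lies outside its remit: only futility is excluded, the planned analysis covers effectiveness, and the board may recommend modification.

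**Conclusion.** The point holds in limited form. The protocol states a directional rule for recommending termination, and the only safety analysis it describes withholds the direction. With pooled data no difference between arms can be seen. With coded arms the difference can be seen but not interpreted until the codes are broken.

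This rests on reading blinded as describing the board's own analysis, which is how the sentence is built, since assessor masking is covered elsewhere. It does not rest on any mortality figure. The rates of 3/5/8% are assumptions, used only to show that by-arm data (about 19/28/45%, one arm against the other two) would detect a doubling only slightly more often than the pooled count (about 14/24/39%).

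The consequence is moderate. The monthly meetings may already give the board what it needs, but the text does not say so. The change is worth making because it is cheap and concerns the safety of young children in a population with acknowledged high mortality.

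**What to change.** In Trial monitoring, stop describing the analysis of safety endpoints as blinded. State instead that the DSMB receives a closed report of deaths and serious adverse events by actual arm, with denominators, at the monthly meetings already planned, and that by-arm results are withheld from the investigators and the masked outcome assessors. Leave the board's remit on effectiveness as it stands.

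If the sponsor prefers coded reports, the text should at least say what blinded means and how and when the board can obtain the codes. The 210-completer trigger is a separate matter and also needs correcting; moving it earlier would not resolve this point, because the analysis would still be blinded.

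The cost is the wording of one sentence and a recurring closed table. The small downside is that someone outside the field team must prepare the tables and keep them confidential. Sample size, visits and the primary analysis do not change.
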